#### Specific calculation schemes for the RT value and accuracy of the 1-back paradigm [39]

The RT value in this study is selected for analysis by the RT value (RT-hit), which is the most common method to evaluate the response. Accuracy is represented by the value of d`. The specific formula is as follows: *d* = *Z*_Hit_ − *Z*_FA_. Among them, *Z*_Hit_ and *Z*_FA_ are converted to *Z* values from the hit rate and false alarm rate according to the POZ conversion table. After calculating the *d* value and RT value of each subject, data were imported into SPASS, and one-way ANOVA was used to compare the differences between the three groups before and after the intervention.

#### EEG data

EEG is widely used in neuroscience research [19]. This study is based on previous EEG studies related to WM [25]. Event-related potentials were selected for analysis to explore changes in electrical activity in the cerebral cortex before and after EA intervention at different frequencies. The target components of ERP are N20, P300, and slow-wave NSW. One-way analysis of variance was used and non-parametric tests were used when variances were uneven. Results need to be Bonferroni corrected.

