Current neuroscience research has found that neural oscillations play an important role in a range of cognitive function [17–21]. For example, electroencephalogram (EEG) recording shows that subjects’ oscillations in theta (3–8 Hz) and gamma (> 30 Hz) band have a special correlation with WM [22–25]. Among them, the oscillations in the theta band are responsible for organizing and arranging WM items in sequence [26]; the oscillations in the gamma band play a role in maintaining WM information [27]. In addition, many experiments have confirmed that transcranial alternating current stimulation (tACS) at theta and gamma frequencies can enhance WM in healthy subjects [18–20].

Compared with tACS, EA is a more mature and widely used clinical treatment therapy. A large number of studies have confirmed the safety and effectiveness of EA in the treatment of post-stroke patients. Collectively, this study will explore the effects of EA in the theta (6 Hz) and gamma (40 Hz) bands on WM of stroke patients and investigate changes of electrical activity in the cerebral cortex before and after intervention.

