### Secondary objectives

(1) Since the central executive system is an important part of WM, the study will observe changes in executive functions. (2) WM is closely related to the patient’s overall cognitive level and ability to daily life. The study will also observe patients’ behavioral memory, overall cognition level, and daily life ability. (3) By using EEG, we recorded the electrical signals of the cerebral cortex of patients during 1-back tasks. Through the analysis of the EEG data, the effects of theta-EA and gamma-EA on the electrophysiological properties of the brain will be investigated and compared with sham EA.

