##### EEG recording

When patients perform a 1-back task, their EEG signals are also recorded. The EEG signals were recorded with a 64-channel brain electrode (Bp) device at a sampling rate of 1000 Hz. All electrodes have sintered Ag/AgCl sensors that snap directly into the hat (total height 3.5 mm). The impedance recorded in the EEG remains below 8 kΩ. The ground electrode (GND) is located at Fz, and the reference electrode (reference) is located at Cz. A vertical eye movement (VEOG) electrode is located 2–3 cm from the left eye and serves as a reference electrode for online recording. Each patient is required to adjust the sitting position during the entire experiment to keep the whole body muscles, especially the facial muscles relaxed, and try not to move.

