#### New BI

Referring to other blind studies, if the calculated confidence interval of the new BI includes zero, we will consider the blind method to be successful in this study.

Currently, we have not any additional analyses due to smaller sample sizes in each group.

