### Outcome measurements selection

*N*-back task, as the primary outcome, is one of the traditionally been used paradigms to explore the neural basis of WM and executive function (EC) [53]. Neuropsychological studies show EC (including shifting, updating, and inhibition) is a core component of WM [54], unlike other simple storage tasks, such as forward digital span task [55]; *n*-back task is regarded as a typical task loading on WM updating [56]. In *n*-back task, participants need to decide whether the current stimulus is the same as the stimulus they saw *n* steps back. The larger the value of *n*, the higher the difficulty level of the test [57, 58]. In the pre-experiment, we booked 9 patients with cerebral infarction and randomly assigned them to the theta-EA group, gamma-EA group, and sham-EA group. The intervention parameters and course of treatment are consistent with this experiment. Before intervention, patients were evaluated 0-back, 1-back, and 2-back. It was found that 6 subjects had difficulty performing 2-back, so only 0-back and 1-back were evaluated after the intervention. The results showed that 0-back has the ceiling effect. Thus, we choose 1-back to assess patients’ working memory. In addition to dealing with behavioral evaluations, analysis of the EEG signals is also an important aspect. Studies have shown that the different components of ERP are closely related to the information processing process of working memory [59]. For example, N2 is related to the maintenance of information [60], and P3 is related to the updating of information and allocation of attentional resource [61]. Hence, we recorded the task status of the patient’s EEG signals to explore the impact of the intervention scheme on the electrical activity of the cerebral cortex, including relative to sham.

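### The EEG plan names N20 where its rationale supports N2, gives two online references, and as an ERP-only analysis cannot test the theta/gamma mechanism behind the two frequencies

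*Protocol article*

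**What the plan says.** **Components.** The EEG data section fixes the endpoints: "The target components of ERP are N20, P300, and slow-wave NSW". The reasons come in the Discussion, under Outcome measurements selection: "N2 is related to the maintenance of information", and "P3 is related to the updating of information and allocation of attentional resource".

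**Reference.** EEG recording places the reference electrode at Cz. It then says of the VEOG electrode, 2–3 cm from the left eye, that it "serves as a reference electrode for online recording".

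**Type of analysis.** The Background bases the two stimulation frequencies on theta and gamma oscillations, for example: "the oscillations in the gamma band play a role in maintaining WM information". The third secondary objective is broader: "the effects of theta-EA and gamma-EA on the electrophysiological properties of the brain will be investigated", with sham as comparator. The EEG data section then chooses the method: "Event-related potentials were selected for analysis to explore changes in electrical activity in the cerebral cortex before and after EA intervention at different frequencies". It names no spectral measure and asks for Bonferroni correction. Under New BI, after all the analyses, stands: "Currently, we have not any additional analyses due to smaller sample sizes in each group".

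**The concern.** The sentence that prespecifies the EEG endpoints contains a component for which the article gives no reason, and it omits the one for which it does. If it stays, an analyst must either follow it and examine a component without a rationale, or report N2 and appear to have switched an endpoint.

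The reference wording matters because ERP amplitude is measured relative to the reference. With two centers, two conflicting instructions could be carried out differently at each site. If the eye electrode were the reference, ocular potentials would be subtracted from every channel as recorded.

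The third part is a mismatch of ambition and method. The active arms are defined by frequency bands because those bands are thought to carry working memory, yet the described EEG analysis measures neither band.

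**Working it through.** No sample size or power figure is involved, so most of the check is a comparison of sections.

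**1. Component names**

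| EEG data | Outcome measurements selection | Match |
|---|---|---|
| N20 | N2 (maintenance of information) | no |
| P300 | P3 (updating, attention) | yes |
| slow-wave NSW | not discussed | – |

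The positive component appears once by ordinal name (P3) and once by latency name (P300). Under the same convention N2 becomes N200. N20 would denote a latency of about 20 ms. This reading assumes that the list uses latency names throughout, as P300 suggests. On that reading, 1 of 3 named targets is wrong.

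**2. Reference**

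Let S_i be the potential at scalp electrode i and R the potential at the online reference. The recorded signal is V_i = S_i − R.

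- If R is the VEOG electrode, each V_i contains the ocular potential with a minus sign.
- After re-referencing to another scalp electrode j: V_i − V_j = (S_i − R) − (S_j − R) = S_i − S_j, so R drops out.

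The harm is therefore recoverable, provided that the reference used is known and the same offline reference is applied at both sites.

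**3. Could the recording support theta and gamma measures?**

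Inputs: sampling rate 1000 Hz (EEG recording); 600 ms stimulus plus 1400 ms blank (Primary outcome); stimulation at 6 Hz and 40 Hz (Background).

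- Nyquist limit = 1000 / 2 = 500 Hz, well above 40 Hz.
- Trial length = 600 + 1400 = 2000 ms, so frequency resolution = 1 / 2 s = 0.5 Hz.
- Cycles per trial: 6 × 2 = 12 at 6 Hz; 40 × 2 = 80 at 40 Hz.

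By sampling rate and trial length, both bands can be analysed. The limit lies in the described analysis, not in the data.

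**4. Price in multiplicity**

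Two bands × two active-versus-sham comparisons = 4 contrasts. The article does not define the Bonferroni family. If it held one test for each of the three ERP targets, the per-test level would be 0.05 / 3 = 0.0167. With four more it would be 0.05 / 7 = 0.0071. As a separate exploratory family, the four contrasts would be tested at 0.05 / 4 = 0.0125, and the ERP tests would stay at 0.0167.

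**The case against.** **N20 is an obvious typing slip.** Its neighbour is P300, and the Discussion pairs N2 with P3, so a reader can see what was meant. N2 and P3 are also introduced there as examples, and the slow wave has no rationale in that section either, so absence from the rationale does not by itself make a target wrong. This stands as to size: it is a small correction. The pairing of N20/P300 with N2/P3 is still a mismatch in the sentence that fixes the endpoints.

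**The reference is stated plainly as Cz.** The VEOG sentence may be a loose description of an eye-monitoring channel, and offline re-referencing removes a common reference in any case. The algebra supports this, and re-referencing is detail that an article may omit. What remains is that the text names two references for the same recording.

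**ERP-only is a choice, not an error.** The article says that ERPs were selected and gives a matching reason. It uses oscillations to justify the stimulation frequencies, not to define an outcome. This stands, so theta and gamma power can only be suggested, not required.

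**Added outcomes cost something.** The trial is already recruiting with 22 patients per arm, and four contrasts tighten a shared Bonferroni threshold. This also stands, and is a reason to keep them in a secondary or exploratory role.

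**Conclusion.** Two items of operative text need correction. N20 conflicts with the article's own N2 rationale and affects one of three ERP targets; it is most likely a slip for N200. The recording section also names two online references. Both are minor in size and almost free to correct.

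The third item is a limitation: as described, the EEG analysis cannot test the oscillatory mechanism that motivates 6 Hz and 40 Hz.

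A reader might infer more, namely that the electrophysiology aim cannot be answered from the data collected. The documents do not support that. The aims in the Background and Secondary objectives speak generally of cortical electrical activity and electrophysiological properties. They promise no band-specific result, an ERP comparison with sham can address them, and the recording carries both bands.

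A reader might also take the sentence under New BI as ruling out spectral EEG. It names no EEG measure, begins with a word that leaves the matter open, and gives a reason (small groups) that fits subgroup or adjusted analyses at least as well.

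The conclusion assumes latency naming in the component list. A fuller plan, not shown, may specify spectral analyses, which makes the third item weaker than the first two. EEG is a secondary outcome, so the primary d' analysis and the sample size are untouched.

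**What to change.** 1. **EEG data:** correct N20 to N2 (N200), so that the named targets agree with the Discussion. Cost: one word, dated before the EEG data are analysed.
2. **EEG recording:** name one online reference for both centers and describe VEOG as an eye channel only. Document the reference used for patients already recorded, so that any difference between centers can be removed by a common offline reference. Cost: one sentence and a check of the recording settings.
3. **Optional:** add task-related theta (3–8 Hz) and gamma (>30 Hz, with an upper limit set in advance) power during the 1-back as secondary or exploratory outcomes, each active arm versus sham and adjusted for baseline. State whether the four contrasts join the ERP Bonferroni family or form their own. Cost: analysis time on EEG already recorded, a stricter threshold if the family is shared, and muscle-artefact control in the gamma band. No new patients or visits are needed. If this is not added, a sentence saying that the EEG analysis will not test the oscillatory rationale would prevent over-reading of the ERP results.

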**Methods:**

After assessing their eligibility, 66 patients with stroke will be enrolled from two Chinese medicine hospitals and randomly divided into theta frequency EA group, gamma frequency EA group, and sham-EA group according to the ratio of 1:1:1. All patients will receive 20 sessions of EA procedures for 4 weeks. Patients in three groups will receive EA at two same acupoints in the head: Baihui (GV20) and Shenting (GV24). The frequency of the three groups of EA is set as follows: 6 Hz (theta-EA group), 40 Hz (gamma-EA group), and no current through the electrodes (sham EA). Patients and assessors will be blinded throughout the entire study. The primary outcome is the performance accuracy of 1-back task which is a frequently used measure of WM in cognitive neuroscience research contexts. Secondary outcome measures will include the response time of 1-back task, the Rivermead Behavioral Memory Test, Trail Making Test, Loewenstein Occupational Therapy Cognitive Assessment Scale, modified Barthel Index, and electroencephalogram (EEG) signals during 1-back tasks. A blinding index will be assessed. Data will be statistically analyzed by one-way ANOVA, at 5% of significance level.

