### Sample size calculation

The primary endpoint was the difference of accuracy (d`) scores respectively at baseline and endpoint between the three groups (gamma-EA group, theta-EA group, and sham-EA group) in the 1-back test for patients with post-stroke. Since we did not have enough previous research as the basis for our estimated sample size, we chose the data collected in the previous pre-experiment to calculate the sample size required for this experiment. The null hypothesis is that *μ*_*i*_ = *μ*_*j*_ = *μ*_*t*_, while the alternative hypothesis is *μ*_*i*_ ≠ *μ*_*j*_ ≠ *μ*_*t*_, where *μ* is the mean difference and *i*, *j*, and *t* denote the sham-EA, gamma-EA, theta-EA group, respectively. Our pre-experimental results of 1-back accuracy (d`) scores show that after treatment, the d` values of the gamma-EA group (2.48 ± 0.32) and the theta-EA group (2.02 ± 0.53) are improved compared with the sham-EA group (1.88 ± 0.60). Using the sample size calculation formula for comparing the average of multiple independent samples in the parallel design, under the assumptions of α of 0.05 and (1-β) of 0.8, a sample size of 18 per group has been calculated. Considering a 20% dropout rate, a total of 66 patients will be enrolled in the trial (22 per group). The specific calculation formula is as follows [38]: *n* = λ/Δ

$$ \Delta =\frac{1}{\sigma^2}\sum \limits_{i=1}^K{\left({\mu}_i-\overline{\mu}\right)}^2\kern0.5em \overline{\mu}=\frac{1}{k}\sum \limits_{j=1}^k{\mu}_j $$

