#### The efficacy analysis will use an intention-to-treat analysis

The results of 1-back evaluation are based on the accuracy and response time as the observation indicators. The evaluation results of RBMT, TMT, LOTCA, and MBI are summarized according to the calculation rules of each scale. The results of each of the above assessments are expressed as mean ± SD. The statistical method uses analysis of variance (assuming a normal distribution) and using Kruskal-Wallis (non-parametric test) to test if it does not meet the normal distribution. The significance level was 95% (*p* values alpha < 0.05 on both sides). If the data is missed, the last observation carried forward method will be applied.

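### Bonferroni for the EEG results is valid, but Holm's step-down version gives the same error control and never rejects less; a cheap improvement for a secondary, exploratory outcome

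*Protocol article*

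**What the plan says.** Under the heading EEG data, the protocol article lists the targets: "The target components of ERP are N20, P300, and slow-wave NSW". The test is named next: "One-way analysis of variance was used and non-parametric tests were used when variances were uneven". The section closes with the correction: "Results need to be Bonferroni corrected". It does not say which tests form the family, and it neither mentions nor excludes a step-down version.

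The status of these tests is clear. The abstract places EEG last among the secondary outcomes ("modified Barthel Index, and electroencephalogram (EEG) signals during 1-back tasks"). The EEG section describes the aim as exploration: "Event-related potentials were selected for analysis to explore changes in electrical activity in the cerebral cortex". The secondary objectives add a comparison of arms: "the effects of theta-EA and gamma-EA on the electrophysiological properties of the brain will be investigated and compared with sham EA". The sample size rests on the 1-back accuracy score alone, and no power is stated for EEG.

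**The concern.** Unqualified, a Bonferroni correction is normally read as the single-step method: with m tests, each p-value is compared with 0.05/m. Holm's procedure orders the p-values and compares the smallest with 0.05/m, the next with 0.05/(m − 1), and so on, stopping at the first failure. Its family-wise error control holds under any dependence between the tests, as Bonferroni's does. It therefore asks for nothing more and can only add rejections. For testing, the method named in the plan is dominated by one that costs nothing extra to run.

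What is at stake is narrow but relevant to the trial's aims. Electrophysiology is in the title, and the discussion of outcome selection links different ERP components to different parts of working memory. Which components change, and not only whether any does, is thus of interest, and Holm helps exactly with the second and third components. The trial is small, so there is little power to give away.

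**Working it through.** **Inputs from the protocol article.** Three arms, 1:1:1; "under the assumptions of α of 0.05 and (1-β) of 0.8, a sample size of 18 per group has been calculated"; 22 per group enrolled; three ERP components; one-way ANOVA.

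**Assumptions, because the article gives no figure.** The family is the three components (m = 3). Effects on real components are equal. Correlation between components is 0 or 0.5.

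**Step 1: the plan's own figure.** The article uses n = λ/Δ with 1-back accuracy means of 1.88 (sham), 2.48 (gamma) and 2.02 (theta).
- Mean of the three: 6.38/3 = 2.127. Sum of squared deviations: 0.0608 + 0.1248 + 0.0114 = 0.1971 (from unrounded terms).
- With σ = 0.60, the largest of the three SDs: Δ = 0.1971/0.36 = 0.5474.
- λ = 9.635 (noncentral chi-square, 2 df, α = 0.05, power 0.80), so n = 9.635/0.5474 = 17.6, rounded up to 18.

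The 18 per group is reproduced. EEG does not enter the calculation, so the choice of EEG correction cannot alter it.

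**Step 2: validity of Bonferroni.** For three independent tests:
- Uncorrected at 0.05: 1 − 0.95³ = 0.1426.
- At 0.05/3 each: 1 − (1 − 0.01667)³ = 0.0492.

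The plan's method keeps the family-wise error below 5%.

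**Step 3: thresholds for m = 3.**
- Bonferroni: 0.0167, 0.0167, 0.0167.
- Holm: 0.0167, then 0.025, then 0.05.

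The first threshold is the same, so the chance of at least one rejection must be the same. The methods part only after a first rejection: a second-smallest p-value between 0.0167 and 0.025, for example, is rejected by Holm and not by Bonferroni.

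**Step 4: size at 80% unadjusted power, 18 per arm (simulation).** Average power per real effect under Bonferroni is about 65%.
- All three components real: 65% becomes 73–75% under Holm, a gain of 8 to 10 points. The chance of showing all three goes from 27–40% to 49–58%. In both ranges the first value is for correlation 0 and the second for 0.5.
- Two real: a gain of 3 to 4 points.
- One real: a gain of about 0.

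At 50% unadjusted power with all three real, 33% becomes 37–39%.

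**Step 5: a second effect assumption.** Here each real component is given the standardised effect of the 1-back score (σ = 0.60), with 20,000 simulated trials per row. At 18 per arm this corresponds to about 78% unadjusted power.

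| n per arm | Correlation | Real effects | Bonferroni | Holm | Gain | At least one rejection (both) |
|---|---|---|---|---|---|---|
| 18 | 0 | 1 | 0.632 | 0.635 | 0.003 | 0.644 |
| 18 | 0 | 2 | 0.629 | 0.668 | 0.039 | 0.865 |
| 18 | 0 | 3 | 0.629 | 0.725 | 0.096 | 0.949 |
| 18 | 0.5 | 1 | 0.631 | 0.632 | 0.001 | 0.641 |
| 18 | 0.5 | 2 | 0.632 | 0.666 | 0.034 | 0.799 |
| 18 | 0.5 | 3 | 0.625 | 0.705 | 0.080 | 0.861 |
| 22 | 0 | 1 | 0.746 | 0.748 | 0.002 | 0.755 |
| 22 | 0 | 2 | 0.750 | 0.787 | 0.037 | 0.940 |
| 22 | 0 | 3 | 0.748 | 0.839 | 0.091 | 0.984 |
| 22 | 0.5 | 1 | 0.749 | 0.750 | 0.001 | 0.757 |
| 22 | 0.5 | 2 | 0.742 | 0.775 | 0.033 | 0.882 |
| 22 | 0.5 | 3 | 0.751 | 0.825 | 0.074 | 0.930 |

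The two middle columns are average power per real effect. Simulated family-wise error was about 0.05 or less for both methods in every setting that contained a null component. The pattern matches step 4.

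**The case against.** The strongest reply is that this is a preference between two valid methods. The plan pre-specifies a conservative correction, states nothing false and contradicts nothing. EEG is exploratory, no decision in the protocol hangs on a second or third significant component, and the limitations section already concedes that the sample is small. The family is not defined and no EEG effect size is given, so every power figure rests on assumptions, and the largest gains need real effects on all three components. Bonferroni also has matching simultaneous confidence intervals, and Holm does not have simple ones.

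Most of this stands, and it sets the severity. Two parts do not remove the point. First, the dominance of Holm does not depend on the family: it holds equally for components, pairwise arm comparisons or any other set. Only the size depends on m = 3, and the pairwise case was not simulated. Second, the plan as written promises no simultaneous intervals for EEG, so the loss on that side is small.

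A reader might infer more: that the plan's correction is wrong, or that it costs the trial its chance of an EEG finding. The documents support neither. The correction controls the error rate (step 2), and the probability of at least one rejection is unchanged (steps 3 and 5). Nor is the unstated family a defect here, since an article commonly leaves that detail to the full protocol or the analysis plan.

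**Conclusion.** The point holds as a low-severity, cheap improvement. The method named for the EEG results is valid but is never better, for testing, than Holm at the same family-wise 5%. With three components as the assumed family, 18 per arm and an assumed 80% unadjusted power, the expected gain in average power per real effect is about 0 points with one real effect, 3 to 4 with two, and 8 to 10 with three. The last figure is the favourable case and should not be quoted alone. The primary outcome, the sample size and every stated figure of the protocol are unaffected.

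**What to change.** Replace the correction sentence under EEG data, before the EEG results are analysed, with:

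> EEG results will be corrected within their family of tests by the Holm (step-down Bonferroni) procedure at a family-wise 5% level, with adjusted p-values reported.

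This wording does not impose a family that the article has not defined.

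The cost is one sentence. Data collection and sample size do not change, and the procedure can be applied by hand to a few p-values. The one downside is the lack of simple matching simultaneous confidence intervals; Bonferroni intervals can still be shown descriptively.
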